**Background**

Asthma is the most common chronic disease in childhood. It is defined as a chronic inflammatory disorder of the airways in which many cells and cellular elements promote airway obstruction and hyper-responsiveness (GINA, 2012). According to the World Health Organization (WHO, 2014), asthma is estimated to affect approximately 253 million people worldwide. Despite advances in biological and pathological research, the prevalence of asthma in children has significantly increased over the past decade (Massingham *et al*., 2014).

Moreover, the economic burden of asthma is increasing. In the US, it is estimated that the yearly cost of asthma in children and adults is around $1.48 billion (Price *et al*., 2013). A decade ago, the total annual asthma expenditure in the UK was determined to be £752.6 million with 8% of costs associated with hospital admission, 13% attributable to general practitioner consultations and 79% due to prescription costs (Gupta *et al.*, 2004).

The British Thoracic Society (BTS/SIGN, 2012) and Global Initiative for Asthma (GINA, 2012) guidelines provide the background definitions for three broad categories of asthma control. They include **controlled** (no nocturnal wakening, infrequent short acting beta 2 agonist (SABA) use e.g. < 2 puffs/week, occasional mild symptoms e.g. with exercise and no exacerbations in last 3 months), **partially controlled** (nocturnal wakening< 3 nights/week, SABA use e.g. < 4 puffs/day, mild limitation in exercise tolerance due to asthma, and 2 or fewer mild exacerbations in the previous 3 months) or **uncontrolled** (nocturnal wakening 4-7 nights/week, SABA use e.g. > 5 puffs/day, limitation in exercise tolerance due to asthma and or significant asthma exacerbations requiring oral steroid, Emergency Department attendance or hospital admission in the previous 3 months). Children who present with partially controlled or uncontrolled asthma can be divided into difficult to treat asthma (DTA) and true severe therapy resistant asthma (STRA) after careful investigation (Hedlin *et al.*, 2012). DTA occurs when asthma is uncontrolled but the impact of concomitant disorders and the basics of asthma care (inhaler technique and adherence) have not been adequately resolved.

Many children with asthma can achieve symptom and disease control by using inhaled corticosteroid (ICS) therapy combined with a long acting B_2_ agonist (LABA) and/or a leukotriene receptor antagonist(LTRA) (International ERS/ATS guideline, 2014). However, a number of children with asthma experience frequent symptoms despite being prescribed high dose ICS (Nagakumar and Thomas, 2013; Hedlin *et al.*, 2014)**.**

Drug delivery by inhalation of various medications is the most common treatment approach for asthma in all patient populations. Inhalation therapy offers rapid onset and improved efficacy compared to systemic drug delivery (Bisgaard, 1997).While ICS therapy is well accepted as the foundation of optimal therapy for most asthma patients, efficacy of the therapy depends on drug being delivered correctly into the lungs and taken on a regular basis as a preventer therapy(Machira *et al*., 2011).

It has been suggested that good inhaler technique is an essential aspect of optimal asthma management. Education on inhaler technique has been shown to improve self- management and adherence to asthma therapy. Evidence is available demonstrating that asthma outcomes correlate with proper inhaler technique and that periodically assessing this treatment aspect has a positive impact on asthma control(Bryant *et al*.,2013; AL-Jahdali *et al*., 2013). Moreover, early and repeated tailored education and follow-up assessment can result in sustained good inhaler technique (Klot *et al*., 2011).However, many asthma clinics treating children are unable to effectively evaluate these important patient treatment variables.

Adherence to pharmacotherapy is also considered an important basic tenet of asthma management. Adherence can simply be defined as the extent to which a patient follows the instructions of the prescriber (Osterberg and Blaschke, 2005).While inhaled therapy technique is an essential feature of asthma pharmacotherapy, some patients with good technique may have poor inhaler adherence. Available data suggest the average medication adherence to ICS in children is only approximately 50% (Fish *et al*., 2001; Osterberg and Blaschke, 2005).

It is known that adherence to ICS in children is a complicated matter influenced by diverse issues including socioeconomic factors, parents’ beliefs about asthma and asthma medications, and poor patient-doctor communication (Osterberg and Blaschke, 2005; Armstrong *et al*., 2014). In addition, parent/guardian health issues such as depression or substance abuse may negatively affect adherence in young children as a result of the parent/guardian’s failure to remind, or assist the child in the use of their medication (Brackis-Cott *et al.*, 2003). Non-adherence to medication can have various negative patient consequences such as more frequent clinic visits, disease exacerbations, hospital admissions, and increased cost of care (AL-Jahdali *et al*., 2013).Indeed, a recent review of childhood asthma deaths in SE England showed that medication non-adherence was a contributing factor in more than 50% of cases, including patients with milder disease (Anagnostou *et al*., 2012)

Despite being an area of active research, many interventions such as isolated educational efforts are ineffective in improving adherence (Drotar and Bonner, 2009).In a qualitative study in the primary care setting, asthmatic children of parents who expressed medication beliefs of a high concern–low need pattern had poor outcomes. Researchers subsequently showed that these beliefs could be modified by repeated tailored education and close follow-up, to result in high medication adherence. They concluded that “it is not the education per se, but rather the intensity, quality and frequency of education about self-management and follow-up that help to improve adherence” (Klot *et al.*, 2011).A multicentre clinical trial in the USA was designed to determine what medication was best to add in children with severe asthma already taking ICS and LABA. Interestingly, the trial was cut short due to an inability to recruit an adequate number of children. Patient improvement while under close supervision during the run in period was the main reason for the lack of patient recruitment. (Strunk *et al.*, 2008)

Different methods used to assess patient adherence to prescribed therapy have resulted in variable outcomes. Adherence can be measured by collecting data from patients or their parent/guardians, pharmacy dispensing records, electronic monitoring devices, or patient observation (Osterberg and Blaschke, 2005).Sincethe approaches have produced variable results, it can be concluded that presently there is no preferred method to effectively measure or improve medication adherence in asthma (Sumino and Cabana, 2013).

Direct observation therapy (DOT) is recommended by the WHO to promote adherence in the management of tuberculosis (TB) and this approach was adopted in 187 countries by 2005 (WHO, 2010). DOT allows assessment of correctly taking and completing therapy, but also can be valuable to promote adherence to medication use. DOT involves a healthcare professional observing patients taking their medication at home or in the clinic (Dosumu, 2001; Otu, 2013).The DOT approach to TB management has been utilised successfully in different countries as this approach has been shown to enhance medication adherence, improve outcomes including microbiologic success, and decrease acquired drug resistance to therapy (Favorov *et al.*, 2012; Walley *et al*., 2001; Pasipanodya and Gumbo, 2013).

While data exist to show that observation of inhaler technique can positively affect asthma management, there are no published studies using a DOT approach as a means to improve medication adherence. However, it has been suggested that using DOT with nurses directly observing asthmatic children’s inhaler technique and adherence, for example at school or home, would be very resource intensive and likely not feasible for continued use (Otu, 2013).

In recent years, there has been widespread use of mobile smartphone and computer devices within the healthcare environment. A recent survey of teenagers and caregivers in urban paediatric practices showed that 84% of respondents were smartphone owners, a finding that was independent of age group, gender, ethnicity, and socioeconomic status (Singh *et al.*, 2014).DeMaio *et al.* (2001) conducted a pilot study that compared videophone telemedicine (V-DOT) to standard DOT (S-DOT) in the treatment of TB. In the videophone group, patients took videos of medication administration that were provided to clinicians involved in their management. The adherence rate was 95% for V-DOT compared to 97.5 % for S-DOT, but personnel time was decreased by 288 hours with V-DOT in only 6 patients. Similarly, a telehealth videophone home monitoring approach to TB was shown to enhance treatment compliance and use less clinic resources in a larger study by Wade *et al.* (2012).

More recently, Creary *et al.* (2014) developed a novel mobile DOT approach utilising smartphone and computer devices that resulted in a median monthly observed adherence of 93.3% over the 6 month trial in children with sickle cell disease. Finally, specific to asthma patients, Vasbinder *et al*., (2013) has developed a study to access the effectiveness of using mobile phone text-messages to remind and encourage non-adherent patients to take their medication and thereby improve control of their disease; results of the study are not yet available. Limited available evidence, therefore, suggests that communication technology could be utilised to achieve therapeutic goals of correct administration technique and improved adherence to therapy in asthma patients while limiting resource utilisation.

**Aims and objectives**

The principal aim of this study is to evaluate the feasibility and clinical impact of a mobile DOT approach (via video capture in the patient’s home) on the administration technique for, and adherence to, ICS in children with partially controlled or uncontrolled asthma. A secondary aim is to determine factors that influence adherence to ICS in children with asthma.

The specific objectives are to:

1. Investigate the feasibility, practicality, and persistence of a mobile DOT technology approach in the home setting to assist with disease management of children and young people with partially controlled or uncontrolled asthma.
2. Assess inhaler technique and adherence to ICS therapy by use of DOT videos, parent/guardian and child self-report questionnaires (Medication Adherence Report Scale (MARS)), pharmacy records and patient’s general practitioner (GP) records.
3. Evaluate the impact of the DOT intervention on asthma clinical outcomes including physician assessment of disease control, medication changes, asthma control tests, health-related quality of life and pulmonary function studies in participating children.
4. Identify parental/guardian and patient factors that influence adherence to ICS in participating children and young people with asthma

**Study design**

A randomised intervention trial will be used. Participants will be randomised to either an immediate (I-med) or a delayed (D-med) mobile technology DOT intervention. Randomisation will be restricted based on two factors including age (categorized as Young Children ages 2 up to 5 years, Children ages 5 up to 12 years and Young People ages 12 up to and including 16 years) and patient gender (Gore, 1981).

Both subject groups will receive standard-of-practice asthma education and management in the Asthma Clinic prior to study enrolment. Participants allocated to the I-med group will take part in the mobile technology DOT intervention for the first 6 weeks. Outcomes will be evaluated at the start (week 0) and end of the 6 week intervention period and during clinic visits at weeks 12 and 18 for follow-up. Those participants allocated to the D-med group will have the DOT intervention started after a 6 week “intervention-free” interval with usual Asthma Clinic care. Outcomes in the D-med group will be assessed at baseline (week 0), week 6 (intervention start), week 12 (end of intervention), and at weeks 18 and 24 for follow-up. (see Figure 1)

**(a) Study site**

Parents/Guardians and their children will be recruited during outpatient appointments at the Belfast Health & Social Care Trust (Royal Belfast Hospital for Sick Children; Community Asthma Clinic).

**(b) Recruitment of participants**

The parents/guardians of children and young people with asthma (aged from2 to16 years) who have continuing symptoms of partially controlled or uncontrolled asthma despite being prescribed ICS therapy will be invited to participate(Invitation letter; Appendix 1). Descriptive information about the study will be provided to both the parent/guardian (Parent/Guardian Information Sheet; Appendix 2) and their children if over the age of 6 years, using age appropriate study information sheets (Appendices 3 and 4). Children will only be included in the study after obtaining written informed consent from their parents/guardians (Appendix 5) and assent from children older than 6 years (Appendix 6). The ability of children to give assent will be determined by their hospital doctor.

**(c) Sample size calculation**

The variability in quality of life (QOL) score changes in a similar population was reported in a pilot study to be 1.3 units (Young *et al.*, 2001). To have an 80% power to detect a statistically significant (P<0.05; two-tailed Student t-test) difference for effect of the intervention between groups of 1 QOL unit would require 36 children per group.

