**DOT intervention trial ***

Immediate group n=36 *asthma education

Delayed group n=36 *asthma education

Week 0 (baseline)

DOT intervention – free for 6 weeks

Start of DOT intervention for 6 weeks

Assessment: Start DOT intervention for 6 weeks

Assessment: stop DOT intervention

week 6

Assessment: stop DOT intervention

Follow- up assessment

week 12

Follow- up assessment

Follow- up assessment

week 18

Follow- up assessment

week 24

* all participants will have received standard asthma education currently used within the Trust before randomisation

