**Data analysis**

Statistical analyses will be conducted by the researcher after entering all data into SPSS (IBM SPSSv.23, USA). All nominal data collected during the study will be analysed using descriptive approaches. Group differences (I-med and D-med groups) will be studied using the independent sample Student t-test. If the data are not normally distributed non-parametric statistics will be utilised (Mann-Whitney U test for independent group differences). A paired Student t-test will be used to detect any differences associated with the study periods within each group

Adherence to ICS use in participants will be determined based on the patients’ general practitioner records of medicine prescribed and the patients’ records of medicine dispensed within the 6 week period, monitoring of video submissions, as well as the total scores achieved from the MARS questionnaires.

Categorical variables associated with non-adherence will be analysed using Chi-squared analysis. If the expected frequency falls below 5, the Fisher’s exact test will be employed.

Factors that affect the adherence to ICS inhaler use will be determined using patient demographic and clinical data together with responses obtained through administration of BMQ, CES-D, MARS, PACQOLQ/PAQOLOQ and ACT/C-ACT questionnaires to the participants and participants’ parents/guardians as appropriate. Multiple regression analysis will be performed to evaluate the relative contribution of different predictors to non-adherence.

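### The sample-size statement does not reproduce: its stated inputs need 28 children per group for 80% power, and 36 per group gives about 90%

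*Protocol*

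**What the plan says.** All the inputs stand in the protocol's section (c), Sample size calculation:

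- Spread: "The variability in quality of life (QOL) score changes in a similar population was reported in a pilot study to be 1.3 units".
- Power: "To have an 80% power to detect a statistically significant" difference.
- Test and level: "P<0.05; two-tailed Student t-test".
- Effect and result: "difference for effect of the intervention between groups of 1 QOL unit would require 36 children per group".

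The Data analysis section names the same test for the comparison of arms: "Group differences (I-med and D-med groups) will be studied using the independent sample Student t-test". Figure 1 carries the result into the design, with "Immediate group n=36" and the same number in the delayed group. Neither the sample-size section nor the figure mentions an allowance for dropout or any other inflation.

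**The concern.** A two-group t-test calculation is fully determined by the spread, the difference, the significance level and the power. The protocol gives all four and then a sample size that does not match them. At least one item in the statement is therefore wrong or missing, and this statement is the protocol's only justification for enrolling 72 children.

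The practical stake is how much loss the trial can absorb. The Feedback questionnaires section foresees participants who upload no videos, stop early or cannot complete the study. If the stated spread and difference are right, 36 per group leaves a margin for such losses. If the calculation really used a larger SD or a smaller difference, 36 is the bare minimum and there is no margin.

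**Working it through.** **Inputs.** From section (c): difference 1 unit, two-sided alpha 0.05, power 0.80, and 1.3 units of variability in score change. The word used is variability, not standard deviation. I read it as an SD because it is given in score units; this is an assumption. Equal allocation comes from Figure 1 (36 and 36).

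**Standardised effect.** d = 1/1.3 = 0.769.

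**Attempt to reproduce 36 at 80% power.**

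- Normal approximation: n = 2 × (1.960 + 0.842)² × 1.3² / 1² = 2 × 7.85 × 1.69 = 26.5, so 27 per group.
- Noncentral t: n = 27.52, so 28 per group. Power is 0.792 at 27 and 0.807 at 28.

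The stated 36 is not reproduced. The gap is 36 − 28 = 8 per group, and 36/28 = 1.29, so the stated size is 29% higher.

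**Power that 36 per group gives.** Noncentral t: 0.896. Normal approximation: 0.904.

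**Which other inputs would give 36?**

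| Reading | n per group |
|---|---|
| As stated, 80% power | 28 |
| 1.3 is a variance | 22 |
| SD multiplied by √2 | 55 |
| Paired test (number of pairs) | 16 |
| One-sided 5% | 22 |
| Alpha 0.025 two-sided | 34 |
| Alpha 0.01 two-sided | 42 |
| Allowance for a Mann-Whitney test | 30 to 33 |
| 85% power | 32 |
| 90% power | 36 (normal approximation), 37 (noncentral t, 36.50) |
| SD 1.35 instead of 1.3 | 30 |

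Rounding of the SD does not explain the gap: an SD of 1.35 needs only 30. Solving for the effect size at 36 per group and 80% power gives d = 0.670. That corresponds to an SD of 1/0.670 = 1.49 with the difference kept at 1, or to a difference of 0.670 × 1.3 = 0.87 with the SD kept at 1.3.

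**Loss allowance.** 28/36 = 0.778, so an allowance of about 22% would lead from 28 to 36. An allowance of 20% gives 28/0.80 = 35.

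**Candidate explanations.** Four remain: a true target of 90% power, an SD near 1.49, a difference near 0.87, or an unstated loss allowance of about 22%. The protocol does not say which applies.

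**Why the choice matters.** With SD 1.3, 28 evaluable children per group give 0.807 power. With SD 1.49, 36 per group give 0.80 and 28 give only 0.69.

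**The case against.** The strongest case on the other side accepts the arithmetic and disputes its weight. On the stated inputs the trial is larger than it needs to be. The protocol calls the study a pilot and names feasibility, practicality and persistence first among its primary outcomes; quality of life is one of several measures in the second area. An oversized group threatens neither the validity of the trial nor its conclusions. This stands, and it is why the point is not a must-fix.

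Three stronger readings are tempting, and the document does not support them.

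- *A reader might infer that the trial is underpowered.* On the stated inputs the reverse holds. Only a different SD or difference would remove the margin, and none is written.
- *A reader might infer that 80% is simply a misprint for 90%.* That fits best numerically, but an SD of 1.49, a difference of 0.87 or a 22% loss allowance leads to 36 as well. The protocol does not show which item is wrong.
- *A reader might infer that 36 could mean either randomised or evaluable children.* Figure 1 sets 36 at the head of each arm, at the week 0 baseline, and its footnote places asthma education before randomisation. So 36 is shown as the allocated size. The open question is narrower: whether the calculation behind 36 already allowed for losses.

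It is also fair to say that 1.3 is never called an SD, and the cited pilot study is not at hand. The variance reading does not rescue the statement, because it gives 22.

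**Conclusion.** The sample-size statement is wrong as written. With 1.3 read as an SD, a difference of 1 unit and a two-sided 5% t-test, 80% power needs 28 per group and not 36, and 36 per group gives about 90% power (0.896). The discrepancy is 8 children per group, or about 10 percentage points of power.

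The conclusion rests on the SD reading, equal groups and complete data. It does not depend on choosing between the normal approximation and the noncentral t, which differ by one child per group. The error is conservative on the stated inputs, so this is a should-fix. Which item is misreported cannot be settled from the protocol.

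**What to change.** First, identify what produced 36: the power, the SD, the difference or an unstated loss allowance. Correct or add that item, and say explicitly whether 1.3 is a standard deviation.

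- **If SD 1.3 and difference 1 stand,** keep 36 per group and restate along these lines: 36 per group give about 90% power with complete data; 28 evaluable per group give 80% power, so about 22% loss, if similar in both groups, can be absorbed. The condition on similar loss is needed. If the same 56 evaluable children were split 36 and 20, power would be about 77%.
- **If another SD or difference was used,** state it and restate the power accordingly. The 28-per-group sentence must not then be used, because with an SD of 1.49 that number gives only about 69% power.

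The cost is wording only, in section (c). Enrolment and Figure 1 do not change.

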**(d) Inclusion/Exclusion criteria**

Inclusion criteria:

1. Children and young people aged from 2-16 years with apparent partially controlled or uncontrolled DTA. The children will have asthma symptoms despite being prescribed ICS (> 400 mcg/day for children < 5 years, 800 mcg/day for children > 5 years) and a second line therapy such as a LABA, LTRA, or theophylline (Nagakumar and Thomas, 2013).
2. One member of the household has access to a smartphone, tablet or other mobile device that is capable submitting a video image to an internet accessible repository. This person must have access to the device for the entire period of the intervention phase (6 weeks) of the study.

Exclusion criteria:

1. Children whose asthma symptoms are controlled.
2. Children and/or parents without access or unwilling to allow use of a suitable mobile device for the study.

Figure 1. Randomized intervention trial of mobile DOT approach in children and young people with uncontrolled asthma.*

